**Methods:**

A prospective multi-centre randomised cross over design trial will be conducted. Forty-seven subjects will be randomised into either Group A or Group B, each with a control and intervention phase. Baseline measurements will be recorded using the Freezing of Gait Questionnaire as the primary outcome measure and 3 secondary outcome measures, the 10 m Walk Test, Timed "Up & Go" Test and the Modified Falls Efficacy Scale. Assessments are taken 3-times over a 3-week period. A follow-up assessment will be completed after three months. A secondary aim of the study is to evaluate the impact of such a device on the quality of life of people with Parkinson's disease using a qualitative methodology.

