## Methods

### Study Design

A randomised cross over design will be used. Forty-seven subjects will be randomised into either Group A or Group B using sealed, computer generated random numbers.

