### Intervention

On Days 1–8 of the trial, the participants in Group A and Group B will be given the iPod, loaded with podcasts. During this period they will familiarise themselves with the functionality of the device i.e. turning the device on and off, increasing and decreasing the volume and inserting the earphones into the ear. They will be instructed to use the device only when sitting at home, and also instructed that the device should not be turned on when walking or performing any mobility related or daily tasks. Investigators will schedule a phone call to check the device is being used properly and that the participant is not having any problems.

On Days 8–15, participants in Group A will be allocated to the 'intervention' phase. Each participant will be given an iPod containing an auditory cue in the form of a continuous metronome beat, individualised to the person's walking frequency (less 10%). Participants will be instructed to listen to the cueing when they are performing any mobility related tasks. They will be encouraged to listen to the rhythmical cue and to try to match their heel strike with the beat of the metronome sound on the device. During this time period, participants in Group B will be allocated to the 'control' phase. Participants will be provided with the iPod shuffle containing no music or metronome beat. Participants will be instructed to continue using the device in a similar manner to that of the first week. On Days 15–23, participants in Group A will be allocated to the 'control' phase and participants in Group B will be allocated to the 'intervention' phase. The progression from screening and enrollment to randomisation is illustrated in Figure legend 1.

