### Outcome Measures

Assessments will be taken 3 times over the 3-week period on days 8, 15 and 23. A follow-up assessment will be completed after 3 months. The primary SOM in this study is the Freezing of Gait Questionnaire (FOGQ) [31]. The severity of freezing of gait is most accurately assessed by the FOGQ. The questionnaire focuses solely on freezing and does not include items relating to falling or festination. The FOGQ has been shown to be both valid and reliable as an outcome measure in people with PD [31].

Secondary outcomes will also be utilised including the 10MWT [32], TUG [33] and the MFES [34]. The 10MWT [32] has been found to be valid and reliable in measuring speed in people with PD and will be used as a measure of gait speed during the different time-points in the study. The TUG [33,35,36] has been used as a tool for measuring basic mobility performance and has been proven to be both valid and reliable in people with PD [35]. The MFES [34], unlike the Falls Efficacy Scale (FES) [34,37], assesses outdoor activities as well as indoor activities and demonstrates greater internal test-retest reliability then the original FES. The MFSE will be used to evaluate any change which may occur in an individuals falling pattern due to auditory cueing.

In addition, the impact of the AC device on the individual and their quality of life with be explored using a semi-structured interview. This interview will be conducted by a person unknown to the participant. All interviews will be audio-recorded.

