### Analysis

All data will be collected on paper and the records will be stored by registration number in a secure cabinet. Anonymised data will be transferred to a computer database and secured using a password. An independent researcher will cross check all entries. Appropriate statistical tests will be carried out on the data using MINITAB Release 13.1.

The purpose of the statistical analysis is to test the hypothesis that there will be a statistically significant difference in freezing, gait speed and number of falls from baseline to post-intervention assessment. Firstly, the participants' demographic details and primary and secondary outcome measure scores will be compared in the two groups at baseline. If necessary, adjustments for baseline variables will be made using analysis of covariance. Analyses will be carried out to examine the difference between the groups with respect to the change in the FOGQ score from baseline to post-intervention assessment. Secondary outcomes will be compared between the two groups using Student's t-test or the Wilcoxon rank sum test for ordinal data. Descriptive statistics will also be used to represent demographic data.

All interviews will be transcribed verbatim and examined in terms of themes according to the method devised by Miles and Hubberman [39]. Firstly, participants responses to each question will be transferred into a Microsoft excel document to facilitate analysis. Following analysis of the responses to each question, a coding system will be developed in order to facilitate the identification of recurrent responses. Three researchers will be provided with the responses to all of the questions in an unencoded format; thereafter they will independently code the responses sequentially using the predefined codes. Any coding disagreements will be resolved through discussion.

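### Read plainly, the primary FOGQ analysis compares Groups A and B when each has just finished cueing, so the device effect cancels and only a period difference remains

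*Protocol article*

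**What the plan says.** Under Study Design the protocol article states: "A randomised cross over design will be used. Forty-seven subjects will be randomised into either Group A or Group B". The Abstract adds that subjects are "randomised into either Group A or Group B, each with a control and intervention phase".

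The Intervention section fixes the order. For the first period: "On Days 8–15, participants in Group A will be allocated to the 'intervention' phase", and for the other group, "During this time period, participants in Group B will be allocated to the 'control' phase". The second period, Days 15–23, reverses this: "participants in Group A will be allocated to the 'control' phase and participants in Group B will be allocated to the 'intervention' phase". One phase follows the other with no gap.

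Outcome Measures names the FOGQ as primary and gives the timing: "Assessments will be taken 3 times over the 3-week period on days 8, 15 and 23", with a follow-up at three months.

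The Analysis section then defines the FOGQ comparison as the "difference between the groups with respect to the change in the FOGQ score from baseline to post-intervention assessment". Shortly before, it uses the same term, the two groups, for the baseline comparison, which can only mean the randomised groups A and B. It does not say which day is the post-intervention assessment.

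**The concern.** In this design, group is an order of treatment and not a treatment. Both groups receive cueing, at different times, and intervention is the protocol's own name for a phase that each group completes. The post-intervention visit is then most naturally the visit that closes that phase: Day 15 in A and Day 23 in B.

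A comparison of A with B at those visits sets one just-cued group against another. A device that works would be expected to show no difference, and a time trend between Day 15 and Day 23 could show one with a device that does nothing. The primary aim is the effect of the device on freezing, so the primary outcome is the one affected.

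**Working it through.** **Inputs.** The sequence order is from the Intervention section, the visit days from Outcome Measures, the contrast from Analysis, and the total of 47 from Study Design. Day 8 is taken as baseline, because it is the first of the three assessments and precedes both phases. The documents give no FOGQ SD, correlation, period effect or carryover.

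**Notation.** Let p1 and p2 be the mean changes from Day 8 to Days 15 and 23 that would occur without the device. Let t be the device effect (negative if freezing lessens), and c the share of t still present in Group A at Day 23.

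| Expected change from Day 8 | Day 15 | Day 23 |
|---|---|---|
| Group A (device, then control) | p1 + t | p2 + ct |
| Group B (control, then device) | p1 | p2 + t |

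**Three readings of the contrast, A minus B**

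1. Each group's own post-device visit (A Day 15, B Day 23): (p1 + t) − (p2 + t) = p1 − p2. No t is left. Carryover does not enter, because A is measured before its control phase and B's control phase came first.
2. Day 23 for both: (p2 + ct) − (p2 + t) = −(1 − c)t. The sign is reversed, because A is then the control group, and the contrast is zero when c = 1.
3. Day 15 for both: (p1 + t) − p1 = t. This is a valid parallel comparison.

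Taking Day 15 as Group B's baseline does not rescue reading 1: without carryover, (p1 + t) − (p2 + t − p1) = 2·p1 − p2.

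**Crossover contrast.** Take Day 15 minus Day 23 within each person. The expectation is p1 − p2 + (1 − c)t in A and p1 − p2 − t in B. Half the difference between the groups is (2 − c)t/2 = (1 − c/2)t. The period effects drop out. The contrast equals t with no carryover, 0.75t at c = 0.5 and 0.5t at c = 1.

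**Illustrative size.** Assumed: 24 and 23 participants, SD 1, within-person correlation 0.7, t = −0.82 SD, two-sample t-tests, 10,000 simulated trials per scenario. The value 0.82 is what a two-group comparison of 47 people detects with 80% power at 5%: (1.96 + 0.84) × √(2/23.5) ≈ 0.82.

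| Contrast | c = 0: mean, rejection | c = 0.5 | c = 1 |
|---|---|---|---|
| Own post-device visit | 0.00, 5% | 0.00, 5% | 0.00, 5% |
| Day 23 for both | +0.82, 95% | +0.41, 42% | 0.00, 5% |
| Day 15 for both | −0.82, 95% | −0.82, 95% | −0.82, 95% |
| Crossover contrast | −0.82, over 99% | −0.62, over 99% | −0.41, 94% |

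With no device effect and a shift of −0.4 SD between Day 15 and Day 23, the own-visit contrast rejected in 41% of trials and the other three in about 5%.

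On the FOGQ scale, assume a within-person SD of 2 or 3 points and groups of 23 and 24. The standard error of the own-visit contrast is √2 × SD × √(1/23 + 1/24), or 0.83 and 1.24. A drift of 2 points between the visits, with no device effect, is then 2/0.83 = 2.4 or 2/1.24 = 1.6 standard errors. The simulated false rejection rates on these assumptions were 65% and 36%.

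The stated sample size cannot be reproduced, because it concerns the TUG and 10MWT and no SD is given. Nothing here depends on it.

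**The case against.** The strongest reply is that the Analysis section names no day, so full cancellation follows from one reading and not from an explicit statement. That stands. A reader might infer that the control phase is never used, or that the trial cannot answer its question. Both hold only on the plain reading: with Day 23 for both groups, A's end-of-control score is the comparator, and with Day 15 for both, B's is. Nor is it enough to say that both groups have had the device by then. That is equally true at a common Day 23, where the effect survives unless carryover is complete. The Power section speaks of a difference between the groups, which suggests that the authors had a treated-versus-control comparison in mind.

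The alternatives still do not rescue the sentence. At a common Day 15, Group B has had no intervention, so post-intervention does not describe its visit, and period 2 goes unused. At a common Day 23 the sign reverses and carryover shrinks the result. The hypothesis stated in the same section, a change from baseline to post-intervention, does keep the device effect, but as a before-after change without a control.

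A second reply is that a condensed article leaves day labels and period terms to a fuller plan. That would answer an omission. Here the article states a contrast, and a plan that followed it would inherit the problem.

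A third is that the obvious crossover remedy has a weakness of its own. That stands too. The Background reports that the effects of cueing outlast the cues, and the Intervention section has no washout, so carryover must be part of any correction.

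**Conclusion.** On the plain reading, the expected value of the stated primary FOGQ contrast is p1 − p2 and does not depend on the device effect. This needs no assumption about SDs, drift or carryover. On the other two readings the contrast is −(1 − c)t or t. One sentence therefore allows zero device effect, a reversed effect or the effect itself, and no reading gives the within-person device-versus-control comparison.

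The rejection rates only illustrate. They rest on assumed SDs, correlation and effect size, and the false-positive figures also need a drift that the documents do not report.

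A reader might also infer that taking Day 15 as a second-phase baseline would count the device effect twice. Without carryover, intervention change minus control change contains 2t in Group A but only t in Group B, so doubling holds for A alone. Day 15 is still unsuitable as a baseline, because in A it is the end of cueing.

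The sentence must be corrected before the primary analysis is run, because it governs the primary outcome.

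**What to change.** Replace the FOGQ sentence in the Analysis section with a named device-versus-control contrast, with stated days and Day 8 as the only baseline. Either option below would do.

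- **Option (i), crossover contrast primary.** Analyse the within-person FOGQ difference, end of device phase minus end of control phase (Group A: Day 15 minus Day 23; Group B: Day 23 minus Day 15), adjusted for period. A linear model with participant, period and condition does this. State that, with no washout and the persistence described in the Background, carryover would bias the estimate toward zero, to half of t if complete. Report the Day 15 comparison of A with B alongside it, since carryover cannot affect that comparison.
- **Option (ii), first period primary.** Compare A with B on the FOGQ from Day 8 to Day 15, adjusted for the Day 8 score, with the crossover contrast as supporting analysis.

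The cost is rewording and a little more analysis, with no new data, visits or participants. Option (ii) gives up some precision. Under the correlation of 0.7 assumed above, the standard error of the unadjusted change comparison is √0.6 × √(1/24 + 1/23) = 0.23 SD, against half of that, 0.11 SD, for the crossover contrast; adjustment for Day 8 recovers a little. The advantage of option (i) falls as carryover grows: at full carryover the two simulated powers were about equal (95% for the first-period comparison, 94% for the crossover contrast), and only the first-period estimate was unbiased.

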## Discussion

Auditory cueing as a physiotherapy intervention is not a new concept; however, the technology to date has not been practically and commercially viable for use in a clinical setting. By lowering the cueing frequency by 10% of the individuals self-selected walking speed, evidence suggests that this may help to normalise Parkinsonian gait patterns in people who freeze.

The iPod and similar devices provide a cost effective and an innovative platform for integration of IACDs into the clinical setting, social and home environments and are shown to have immediate effect on gait, with improvements in walking speed, stride length and cadence. It is evident that IACDs are of benefit to people with PD and the aim of this RCT is to maximise the benefits by allowing the individual to use devices in both a clinical and social setting, with minimal disruption to their daily routine.

## Conclusion

The self-report questionnaires will allow researchers deeper insight into the impact of IACDs on patients. By establishing evidence based interventions such as described in this protocol, can we strive to reduce the impact of PD related motor symptoms on the individual.
